#### mRS scores

0 - no symptoms, 1 - no significant disability, carrying out all usual activities normally while experiencing some symptoms, 2 - slight disability, self-sufficient in taking care of basic needs but without the skills to complete all previous activities, 3 - moderate disability, requires some help, but able to walk unassisted, 4 - moderately severe disability, incapable of attending to own bodily needs without assistance, and unable to walk unassisted, 5 - severe disability, needs constant nursing care and attention, incontinent, and bedridden, 6 - deceased.

#### Secondary outcomes

The secondary outcome measures were all-cause mortality at 30 days, 6 months Montreal cognitive assessment (Mo-CA), delayed cerebral ischemia, the serum PPAR- γ levels at 1, 3 and 7 days after operation. duration of hospitalization, pulmonary and cardiovascular complications, rebleeding, intensive care unit stay, the incidence of sepsis, the occurrence of hydrocephalus, and treatment modality used to treat the hydrocephalus.

#### Mo-CA

Long-term cognitive function is assessed with the Montreal cognitive assessment (MoCA) (Ozdilek and Kenangil, 2014). The MoCA is rated on a scale ranging from 0 to 30 points. The MoCA threshold of 26 points is used to diagnose cognitive impairment and a score of less than 22 is considered to indicate serious cognitive impairment (the optimum threshold score for cognitive domain impairments according to the MoCA) (Wong et al., 2015).

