### Follow-up

The follow-up duration will be 6 months and 12 months beginning from the time when patients were randomized. Patients will be contacted by phone and asked to come back to the hospital for further examinations, which will include conventional CT scans, transcranial Doppler ultrasonography, and neurological scale evaluations. If a patient cannot be located for follow-up, the most recent data evaluated will be used to determine the patient’s values for the 6-month follow-up (Table 1).

**TABLE 1 T1:** Outcome measures and measurement points.

Visit number	Screening period	Follow-up period		
	1	2	3	4
Research arrangement	Screening	In-hospital	30 days	6 months
Informed consent	√			
Selection criteria	√			
Baseline information	√			
General history	√			
Symptoms and physical examination	√			
GCS grading	√			
WFNS grading	√			
Hunt-Hess grading	√			
Conventional brain CT	√	√		
Transcranial Doppler	√	√		
Electrocardiogram	√	√		
Blood sugar	√	√		
Blood NT-proBNP	√	√		
All-cause mortality			√	
mRS score			√	√
Mo-CA			√	√
End point evaluation		√	√	√
Adverse event evaluation		√	√	√
Complications		√	√	√
Intensive care unit stay		√	√	√
Length of hospital		√	√	√
Hospitalization costs		√	√	√

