### Sample size estimates

According to previous clinical data and our pilot study’s preliminary experiments, 51.9% (42/81, retrospective data) of patients in the untreated group had a good clinical outcome compared with 63.3% (19/30) in the intervention group. The decision to recruit 378 patients (189 in each arm) was based on a power analysis with an alpha of 0.05, a statistical power of 80%, and a 10% loss to follow-up. We decided to enroll 400 patients (200 in each arm). All of the data from the study’s baseline as well as its outcomes were input into the database by a research nurse. The analysis of the data was performed by the research coordinator. The CTDMC checked the data and discussed the findings.

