### Statistical analysis

SPSS 20.0 will be utilized for the analysis of all the data. Measurement data will be expressed as the mean ± SD. After the first half of the patients were recruited, CTDMC evaluated the safety of the trial participants, efficacy, and overall progress of the study and did a masked interim analysis. All patients assigned a random number during the randomization process will be examined using an intention-to-treat analysis. If any measurements in the medical records or outcome measures are found to be incomplete during the statistical analysis, the final data obtained will be considered the final result for use in the statistical analysis.

Two-sample t-tests and odds ratios (OR) with 95% confidence intervals (CI) are provided to identify variations across treatment groups. The criterion for statistical significance will be set at *p* < 0.05. Adjusted odds ratios (aORs) will be calculated using multivariate logistic regression to account for the impact of the treatment facility and any variations in baseline variables for the primary and secondary outcomes. We also did per-protocol and as-treated analyses.

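### The rule of using the last data obtained fails at 6-month Mo-CA for survivors too impaired to be tested, and can bias this secondary comparison

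*Protocol article*

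**What the plan says.** The Secondary outcomes section lists "all-cause mortality at 30 days, 6 months Montreal cognitive assessment (Mo-CA), delayed cerebral ischemia" among others. The Mo-CA section describes the scale ("The MoCA is rated on a scale ranging from 0 to 30 points"), with a threshold of 26 for impairment, and adds that "a score of less than 22 is considered to indicate serious cognitive impairment". Table 1 schedules Mo-CA at 30 days and at 6 months.

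Two rules cover missing values:

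- Follow-up section: "If a patient cannot be located for follow-up, the most recent data evaluated will be used to determine the patient’s values for the 6-month follow-up".
- Statistical analysis section, for any incomplete measurement or outcome: "the final data obtained will be considered the final result for use in the statistical analysis".

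The Statistical analysis section also commits to intention-to-treat for everyone randomised, and offers two-sample t-tests and odds ratios for group comparisons. It does not say which of the two applies to Mo-CA.

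The mRS scores section defines a living state in which testing will often be impossible: "5 - severe disability, needs constant nursing care and attention, incontinent, and bedridden".

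**The concern.** Mo-CA is a performed test. A patient who is unresponsive, aphasic or otherwise unable to cooperate may be alive, located and in follow-up, and still produce no score. The article's general rule then needs an earlier score, and the only earlier Mo-CA in Table 1 is the one at 30 days.

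This missingness is not incidental. Who can be tested depends on neurological recovery, which is what the drug is meant to improve. If treatment makes some patients just well enough to be tested, they enter the pioglitazone scores, probably near the low end, while their counterparts on placebo contribute nothing. An effective drug could then look neutral or worse on cognition. The group left out is also the group most informative about severe cognitive loss.

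**Working it through.** **Following the rules as written for a living, located patient**

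| 30 days | 6 months | Value under the stated rule |
|---|---|---|
| untestable | untestable | none: drops out, contrary to intention-to-treat |
| tested | untestable | 30-day score, from before the loss of testability |
| either | tested | 6-month score |

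The Follow-up rule does not help in the first two rows, because these patients have been located.

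**Inputs.** The documents give no Mo-CA mean, SD, mortality or untestable share, so there is no figure of the plan's own to reproduce. Assumed for illustration: survivors' latent Mo-CA is normal with mean 21 and SD 6, clipped to 0-30; deaths *d* are equal in both arms; untestable survivors are *u*; 200 patients per arm (from the Sample size section); no drug effect on the score of any patient. All untestable survivors are omitted (the first row only).

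Plausibility of *u*: the planning figures are "51.9% (42/81, retrospective data) of patients in the untreated group had a good clinical outcome compared with 63.3% (19/30) in the intervention group", so mRS 4-6 is 100 - 51.9 = 48.1% in control. With *d* = 20%, 28.1% are alive with mRS 4-5; with *d* = 25%, 23.1%. The control values of *u* below fit inside these.

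**Formulas.** Fraction of survivors removed = *u*/(1 - *d*). Tested *n* = 200(1 - *d* - *u*). *D* = difference in means of the remaining scores (pioglitazone minus placebo). SE = √(v_c/n_c + v_p/n_p). Chance of a significant result against the drug = Φ(-1.96 - *D*/SE).

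**Results if the least able survivors are exactly the untestable ones**

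| *u* control vs drug, *d* | tested *n* | *D* | *D*/SE | apparent harm |
|---|---|---|---|---|
| 15% vs 9%, 20% | 130 vs 142 | -0.68 | -1.28 | Φ(-0.68) = 25% |
| 10% vs 5%, 20% | 140 vs 150 | -0.61 | -1.11 | Φ(-0.85) = 20% |
| 20% vs 10%, 25% | 110 vs 130 | -1.16 | -2.18 | Φ(0.22) = 59% |

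**Sensitivity**

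- *Looser link between cognition and testability.* With correlation 0.7 the three chances fall to 12%, 10% and 24%. With 0.5 they are 7%, 7% and 13%, and *D* is -0.33, -0.30 and -0.57. The nominal value is 2.5%.
- *Smaller shift.* 15% vs 12% with the exact cut gives -0.33 points and 9%.
- *Benefit in testable patients.* Adding 0.75 points brings the first two rows to about zero (-0.68 + 0.75 = +0.07; -0.61 + 0.75 = +0.14). Adding 1.5 points makes all three positive.
- *Cut-off instead of mean.* In the first row, the share of tested patients scoring 22 or more falls from 53.4% to 48.9% although nobody is worse off. Over all randomised patients it is 0.534 × 130/200 = 34.7% and 0.489 × 142/200 = 34.7%: the artefact disappears.

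**Cross-check with a simpler model.** Assume 15% dead, 20% of controls untestable, tested mean 23, SD 5, and 5% of the drug arm becoming testable with mean 12. Drug mean = (0.65 × 23 + 0.05 × 12)/0.70 = 22.21, so *D* = -0.79. Shifts of 3% to 11.4% and newly testable means of 8 to 20 give -0.13 to -2.24. Scoring untestable survivors at 0 turns the sign: 0.05 × 12/0.85 = +0.71 in the central case, +0.28 to +2.68 over the range.

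The effect of the carried-forward 30-day scores (second row of the first table) was not modelled.

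**The case against.** A reader might infer that the plan has no scoring rule at all for untestable patients. The documents do not support that. This is a condensed article, and the coding of untestable patients may sit in an SAP that is not shown. The article also states a rule, which gives a value to anyone tested at 30 days. What stands is narrower: the stated rule gives nothing to one group and an outdated score to another, and an SAP that follows it would inherit both faults.

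A reader might also take the planned mRS difference, 63.3 - 51.9 = 11.4 points, as the share of patients made testable. It is not. The boundary between mRS 3 and 4 is defined by walking and bodily needs, and mRS 4-6 includes death. The end of the cross-check at -2.24 points uses that whole shift and should not be relied on.

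Finally, a reader might infer that apparent harm is likely. The 59% needs a sharp cut on cognition, under which no tested control scores below about 17 points, together with omission of every untestable survivor and no benefit in anyone already testable. Untestability also comes from aphasia or motor deficit, and the drug is being tested as a neuroprotectant, so a benefit in testable patients is the trial's own hypothesis. These objections shrink the size but do not remove the mechanism.

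The article does not fix a mean comparison for Mo-CA. That does not rescue it, since a cut-off among tested patients is affected too.

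**Conclusion.** The point holds against the rule the article states. Carrying the last value forward does not produce a valid 6-month Mo-CA for living patients too impaired to be tested, and leaving out those never tested breaks the intention-to-treat comparison in a way that depends on treatment effect.

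The bias can run against an effective drug if three things hold: untestable survivors are left out, newly testable patients score below the rest, and benefit among those already testable is too small to compensate. The size cannot be derived from the documents. Over the three assumed scenarios and correlations from 0.5 to an exact cut, it is about -0.3 to -1.2 points, with a 7% to 59% chance of apparent harm; smaller shifts in testability give less.

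Mo-CA is one of several secondary outcomes, and the primary mRS analysis, which scores every level of disability and death, is unaffected. It is worth correcting because the correction is cheap and cannot be done well after unblinding.

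**What to change.** In the Statistical analysis section, exempt Mo-CA from carry-forward when a patient is not tested at 6 months because of neurological condition. Then:

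- Compare the proportion of all randomised patients with 6-month Mo-CA at or above one named protocol threshold (26 or 22), counting untestable survivors and deaths as below it. Alternatively, use a rank test with untestable survivors at the bottom of the scale and deaths ranked below them.
- Record the reason for each untested patient on the Mo-CA form.
- Report the mean among tested patients, with the number tested per arm, as a supporting description.

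The cost is a few sentences of analysis wording and one reason code, to be settled before unblinding because reasons for not testing are hard to reconstruct later. The downside is that the Mo-CA result becomes a composite that partly reflects severe disability and death, so it overlaps with mRS and is no longer a simple difference in points. Patients untested for other reasons are not covered by this change.

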### Follow-up

The follow-up duration will be 6 months and 12 months beginning from the time when patients were randomized. Patients will be contacted by phone and asked to come back to the hospital for further examinations, which will include conventional CT scans, transcranial Doppler ultrasonography, and neurological scale evaluations. If a patient cannot be located for follow-up, the most recent data evaluated will be used to determine the patient’s values for the 6-month follow-up (Table 1).

**TABLE 1 T1:** Outcome measures and measurement points.

Visit number	Screening period	Follow-up period		
	1	2	3	4
Research arrangement	Screening	In-hospital	30 days	6 months
Informed consent	√			
Selection criteria	√			
Baseline information	√			
General history	√			
Symptoms and physical examination	√			
GCS grading	√			
WFNS grading	√			
Hunt-Hess grading	√			
Conventional brain CT	√	√		
Transcranial Doppler	√	√		
Electrocardiogram	√	√		
Blood sugar	√	√		
Blood NT-proBNP	√	√		
All-cause mortality			√	
mRS score			√	√
Mo-CA			√	√
End point evaluation		√	√	√
Adverse event evaluation		√	√	√
Complications		√	√	√
Intensive care unit stay		√	√	√
Length of hospital		√	√	√
Hospitalization costs		√	√	√

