### Outcome measures

#### Primary outcomes

Clinical outcome at 6 months and 12 months post-randomization is the primary endpoint measure evaluated using the modified Rankin Scale (mRS) through a standardized interview (Wilson et al., 2005). Research physicians blinded to treatment assignment performed all evaluations. Medical doctors conducting research were instructed on how to undertake the structured face-to-face interview to calculate the mRS score as per standard operating procedures (SOPs). Clinical outcomes were classified as good (mRS 0–3) or poor (mRS 4–6) after the scores were recorded.

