### Trial quality assurance and control

Quality control and assurance will be handled by CTDMC. A clinical research associate who has been assigned by the sponsor will make regular hospital visits to check that the study is conducted according to plan and that all data are being collected accurately. Before, during, and after the experiment, the investigators will follow SOPs for clinical studies. Inspectors will check case registration forms to ensure accurate and complete information throughout the trial. Researchers will receive training that will standardize their data collection and evaluation practices. To guarantee accurate and trustworthy data, researchers will meticulously document all data on case report forms. Researchers will compare aberrant lab test findings to normal reference ranges. To guarantee that the inferences are valid and based on the original data, we will double-check all of our observations and findings. Relevant data management procedures will be implemented throughout the stages of clinical trials and data analysis. Active measures will be taken to control the dropout rate to within 20%.

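### The primary mRS is described only as a face-to-face interview at a hospital return visit, so a reachable patient who cannot travel would be analysed on an old score rather than a current one

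*Protocol article*

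**What the plan says.** The Primary outcomes section sets the endpoint: "Clinical outcome at 6 months and 12 months post-randomization is the primary endpoint measure evaluated using the modified Rankin Scale (mRS) through a standardized interview". It adds that "Research physicians blinded to treatment assignment performed all evaluations", and that these physicians were "instructed on how to undertake the structured face-to-face interview to calculate the mRS score". Scores are then split into good (0-3) and poor (4-6).

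The Follow-up section describes how patients reach that interview: "Patients will be contacted by phone and asked to come back to the hospital for further examinations". The neurological scales are listed there among the procedures of that visit, together with CT and transcranial Doppler. The call brings the patient in; it is not described as a way to collect the outcome.

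The mRS scores section defines grade 4 as including inability to walk without help, grade 5 as "severe disability, needs constant nursing care and attention, incontinent, and bedridden", and grade 6 as death.

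Two rules deal with missing values. The Follow-up section carries the latest assessment forward to 6 months for a patient who cannot be traced. The Statistical analysis section is broader: where outcome measures are incomplete, the last data obtained become the final result, and all randomised patients are analysed by intention to treat. Table 1 schedules the mRS at 30 days and at 6 months, so the only earlier scheduled score is the one at 30 days.

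**The concern.** Among survivors, the poor side of the cut consists of exactly those patients for whom a hospital visit is hardest. Whether a current score is obtained therefore depends on the outcome being measured.

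A patient who is reached by telephone but cannot travel has been located, so the Follow-up rule does not apply and the general last-value rule does. The 6-month primary outcome would then be a score about five months old, although someone who knew the patient's present state was on the line. At 12 months the carried value could be older still. Recovery and late deterioration after day 30 are what a 6- or 12-month endpoint is meant to capture, and a carried 30-day score misses both.

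**Working it through.** **Inputs from the article.** Good-outcome rates used for planning: 42/81 = 51.9% and 19/30 = 63.3%, a difference of 11.4 points. Cut: 0-3 versus 4-6. No attendance rate, mortality split or 30-day to 6-month trajectory is given, so every such value below is an assumption. There is no stated figure on this point to reproduce.

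**1. What the plan's own rule does.** Let g be the true good share in an arm, s the share alive with mRS 4-5, m and k the non-attendance fractions in those two groups (m for mRS 4-5, k for good), a the fraction of mRS 4-5 non-attenders who were 0-3 at 30 days, and b the fraction of good-outcome non-attenders who were 4-5 at 30 days. With deaths known and the last value carried forward:

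error in the observed good rate = s·m·a − g·k·b.

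The first term is undetected deterioration, the second undetected recovery. The sign is open, and a and b are unknown. For scale, assume 15-25% deaths at g = 51.9%, so that s = 33.1% to 23.1%. At m = 0.3, non-attenders with mRS 4-5 number 9.9 to 6.9 per 100 randomised; at m = 0.1, 3.3 to 2.3. Only those who had crossed the cut since day 30 are misclassified.

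**2. Complete-case illustration.** This is not the plan's rule, but it shows how far uneven attendance could move the comparison if non-attenders were left out. Observed good rate = g / (100 − m·s), with everyone else observed. Assume no drug effect (g = 51.9 in both arms), 30% non-attendance among mRS 4-5 in one arm and 10% in the other:

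| Deaths (assumed) | s | m = 0.3 | m = 0.1 | Spurious difference |
|---|---|---|---|---|
| 15% | 33.1 | 51.9/90.07 = 57.6% | 51.9/96.69 = 53.7% | 3.9 points |
| 25% | 23.1 | 51.9/93.07 = 55.8% | 51.9/97.69 = 53.1% | 2.6 points |

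**3. Same attendance pattern in both arms.** Assume control deaths of 15-25% (treated deaths in proportion to the poor share), 5% of good-outcome patients missing, and 10-40% of mRS 4-5 survivors missing. On complete cases the difference moves from 11.4 to between 10.8 and 11.4 points. At the extreme (15% deaths, 40% missing), control is 49.3/84.2 = 58.6% and treated is 60.1/86.7 = 69.3%, a difference of 10.8 points before rounding the rates.

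**4. A drug that only moves patients from death to mRS 4-5.** Assume deaths of 25% versus 15%, good rates equal at 51.9%, 5% of good-outcome patients missing, and 10-40% of mRS 4-5 survivors missing. Complete cases show a spurious 0.6 to 2.7 points in favour of treatment. This route needs no difference in attendance between arms at a given grade.

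**The case against.** The strongest reply is that nobody is lost from the analysis. The last-value rule keeps every randomised patient. A survivor who is bedridden at 6 months was plausibly also mRS 4-5 at 30 days, in which case the carried score gives the right category. That stands, and it limits the harm to patients who changed category after day 30.

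It also disposes of three stronger inferences:

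- A reader might infer that non-attenders drop out and that good-outcome rates are overstated in both arms. The last-value rule keeps them in, so neither exclusion nor that direction of error follows.
- A reader might apply non-attendance to all poor outcomes. With 30% versus 10% this gives 51.9/(51.9 + 48.1 × 0.7) = 60.7% against 51.9/(51.9 + 48.1 × 0.9) = 54.5%, a gap of 6.1 points. But poor includes mRS 6, and a death needs no visit.
- A reader might take the 20% dropout ceiling in the quality assurance section and claim that telephone rating would cut the standard error by about 11% (√0.8 = 0.894). That assumes complete cases and that every dropout can be reached by telephone. The article supports neither, and the sample size section allows for 10% loss.

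A second reply is that the article says only "instructed on how to undertake the structured face-to-face interview to calculate the mRS score as per standard operating procedures (SOPs" and forbids no other mode, so the SOPs, which are not shown, may contain a fallback. This is fair: exclusivity is inferred from the one mode named. If a fallback exists, the two sections need only state it. Third, blinding makes a threefold difference in attendance between arms at the same outcome unlikely, and nothing in the article points to one. Finally, a single face-to-face mode is a legitimate choice for consistency of rating. It is weaker when the stated alternative is a score that may be months old.

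**Conclusion.** The point holds as a cheap improvement. As written, a reachable patient who cannot travel has no current primary outcome recorded, and a score that by Table 1 dates from day 30 takes its place. The consequence is misclassification, in either direction, of patients who crossed the cut after day 30.

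The size cannot be computed from the documents. With similar attendance in both arms the treatment contrast barely moves. Even the deliberately uneven illustration (complete cases, deaths known and assumed at 15-25%, 30% versus 10% non-attendance among mRS 4-5) gives only about 2.6 to 3.9 points. That lower attendance goes with mRS 4-5 is an inference from the grade definitions; no attendance data are given. No change to the sample size follows.

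**What to change.** In the Primary outcomes and Follow-up sections, state that when a patient cannot return, a blinded assessor takes the mRS by telephone with the same structured interview, from the patient or a caregiver. Record the mode of each assessment and report a sensitivity analysis by mode. In the Follow-up and Statistical analysis sections, limit the last-value rule to patients for whom neither route gives a score.

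The cost is a few sentences of protocol and SOP wording and brief training of assessors in telephone and caregiver rating. The call to the patient is already planned, though the article does not say who makes it, so a blinded assessor must be assigned to the interview. The downside is small: telephone and caregiver ratings may differ slightly from face-to-face ratings, which the analysis by mode would examine.
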